### Statistical analysis

An intention-to-treat analytical approach will be used for all outcomes. Descriptive statistics for baseline variables will be calculated to describe the baseline status of the treatment groups. For the primary outcome variable PTS, a logistic regression analysis initially adjusted only for center will be used to compare the incidence rates between the active vs. inactive stockings groups. In secondary analyses, other covariates that will be adjusted for are duration of anticoagulation with warfarin, recurrent ipsilateral DVT during follow-up, temporary use of active stockings, initial type and duration of heparin anticoagulation, co-morbid conditions that could lead to leg symptoms/signs and differences in pertinent baseline variables. The number needed to treat for benefit will be calculated. As an adjunct to the primary analysis, a secondary explanatory (per-protocol) analysis will be performed as well. Subgroup analyses by age, sex, level of compliance, duration of warfarin anticoagulation and recurrent VTE during study follow-up are also planned.

For the secondary outcomes valvular reflux, recurrent VTE, death from VTE, venous ulcer, major bleeding, and severity of PTS, rates in the two intervention groups will be described, and between-group differences explored in similar regression procedures. For differences in mean quality of life scores between intervention groups, analysis of variance incorporating treatment and center will be used. A difference of 4–5 points between groups is considered to be clinically meaningful. Analysis of covariance with adjustment for age, sex and comorbidity will also be used to compare quality of life between groups. For the biomarker variables, univariate analysis will be used to determine the strength of association between each biomarker variable and the occurrence of PTS. For genetic markers, heterozygotes and homozygotes will be analyzed together, given the rarity of homozygotes. IgG, IgM and lupus anticoagulant results will be dichotomized as normal or abnormal. Factor VIII, D-dimer and markers of inflammation will be analyzed both as continuous data and as proportion of values exceeding the upper 90^th ^percentile. For binary and nominal data, the appropriate chi-square tests will be used to examine the respective crude associations, and for continuous variables, the unpaired 2-tailed t-test. To examine adjusted associations, multiple logistic regression analyses will be performed in which the dependent variable is the presence of PTS. The independent variables to be tested are markers of thrombophilia, D-dimer, and levels of CRP, IL-6, IL-8 and MCP-1. Other variables of interest (for interaction and/or confounding) are age, sex, ethnicity, comorbid illness, allocation to active ECS, type and duration of heparin and warfarin use, type of DVT (unprovoked vs. secondary; anatomic extent of DVT), and recurrent DVT during follow-up. The analyses will aim to (1) identify the strength of the association between relevant biomarkers, other relevant explanatory variables and PTS; and (2) explore relevant interactions. Similarly, multiple linear regression will be performed in which the dependent variable is the severity of PTS, as measured by the Villalta scale.

An interim analysis for efficacy will be performed when half of the subjects have completed 2 years of follow-up. The analysis plans call for a Lan-DeMets alpha spending approach with an O'Brien Fleming boundary [70].

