** *Enrollment visit* **
• The nurse completes the baseline form (inclusion/exclusion criteria, demographic and clinical variables, results of objective tests for DVT), PTS scale and pain scale
• The patient self-completes the QOL form
• The nurse performs the leg measurements to size the stockings
• The nurse teaches patients how to apply (using a plastic leg model) and care for stockings (handling, washing), and reinforces the importance of daily use
• Study stockings are supplied to the patient (within a few days after enrollment)
• A venous blood sample is taken for markers of inflammation

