### Sample size and power calculations

We hypothesized that event rates (i.e. PTS at 2 years) will be 30% in the inactive stocking vs. 20% in the active stocking group, i.e. a risk reduction of 33%. Our baseline event rate and effect size for the stocking group were based on a systematic review of available published data [68]. The total sample size required to detect this difference in event rates with a two-tailed α of 0.05 and 80% power is 600 [69]. We increased our sample size to 800 to take into account a projected 25% loss-to-follow up by 2 years.

For the biomarker analyses, our sample size provides > 80% power to detect ORs of 0.5 or lower, or 2.0 or higher. Larger alternatives will be associated with increased power. With regard to inflammatory markers, the analysis will be largely exploratory, as this study will be among the first to provide prospective data on levels of markers of inflammation in patients with DVT and PTS. However, the study design provides power of at least 80% to detect differences on the order of 1/3 of a standard deviation or larger between initial values of inflammatory markers in the two allocation groups.

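### The primary PTS model is valid but adjusts only for center; prespecifying the PTS score already taken at enrollment is a cheap improvement that may add power

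*Protocol article*

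**What the plan says.** The Statistical analysis section of the protocol article fixes the primary comparison: "a logistic regression analysis initially adjusted only for center will be used to compare the incidence rates between the active vs. inactive stockings groups". Further covariates are kept for additional models: "other covariates that will be adjusted for are duration of anticoagulation with warfarin, recurrent ipsilateral DVT during follow-up, temporary use of active stockings". After these three items the list goes on to name "initial type and duration of heparin anticoagulation, co-morbid conditions that could lead to leg symptoms/signs and differences in pertinent baseline variables".

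For the secondary outcomes, PTS severity among them, "rates in the two intervention groups will be described, and between-group differences explored in similar regression procedures". No enrollment score is named there either.

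Table 1 lists what is recorded when a patient enters the trial: "The nurse completes the baseline form (inclusion/exclusion criteria, demographic and clinical variables, results of objective tests for DVT), PTS scale and pain scale". According to the same table, the study stockings reach the patient a few days later, so both scores precede treatment.

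The Sample size section assumes that "event rates (i.e. PTS at 2 years) will be 30% in the inactive stocking vs. 20% in the active stocking group", and the total required "with a two-tailed α of 0.05 and 80% power is 600". This is raised to 800 for a projected 25% loss.

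**The concern.** The primary outcome is patient-reported leg pain and swelling of a typical pattern, present six months or more after the DVT. The enrollment PTS and pain scales record leg symptoms in the same limb before the intervention starts. If they predict later PTS, including one of them in the logistic model increases the power of the treatment test and removes the effect of chance imbalance in initial leg symptoms. The plan collects the scores but does not use them this way.

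The secondary models do not fill the gap. They name several covariates, but the open-ended item is "co-morbid conditions that could lead to leg symptoms/signs and differences in pertinent baseline variables". On its plain reading, its last part brings in a baseline variable because the arms turn out to differ on it. A strong predictor that happens to be balanced would be left out and its precision lost, while a weak one that happens to be imbalanced would be put in. The choice is also made after the data are seen.

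At stake is efficiency in a trial planned with little margin above 80% power, and how far the adjusted analysis is fixed in advance. The validity of the primary test is not at stake.

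**Working it through.** **Inputs from the article.** Event rates 30% (inactive) and 20% (active); two-sided alpha 0.05; power 80%; 600 evaluable; 800 enrolled; 1:1 allocation.

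**Assumption.** The article gives no figure for how well the enrollment score predicts PTS. It is varied here as an odds ratio per standard deviation from 1.0 to 3.0.

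**Step 1: reproduce the plan's figure.** With pooled variance and mean rate 0.25:

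n per arm = [1.96·√(2·0.25·0.75) + 0.8416·√(0.21 + 0.16)]² / 0.10² = (1.2002 + 0.5119)² / 0.01 ≈ 293.2, so 294 per arm and 588 in total.

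This is within 3% of the stated 600. The loss allowance also checks: 600 / (1 − 0.25) = 800. Power at 300 per arm is Φ[(0.10·√300 − 1.2002) / 0.6083] = Φ(0.874) = 80.9%. The planned test meets its own target without any covariate.

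**Step 2: power with one enrollment score added.** Simulation of 6,000 trials per row, 300 per arm, marginal risks held at 30% and 20%, one standard normal baseline covariate, Wald test from logistic regression with and without it. Center effects were not simulated. The Monte Carlo standard error of each power is about √(0.8·0.2/6000) = 0.5 points.

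| Assumed odds ratio per SD | AUC | R² | Power without | Power with | Conditional treatment odds ratio |
|---|---|---|---|---|---|
| 1.0 | 0.50 | 0.000 | 80.7% | 80.4% | 0.583 |
| 1.25 | 0.56 | 0.009 | 80.7% | 81.1% | 0.580 |
| 1.5 | 0.61 | 0.030 | 80.4% | 81.2% | 0.574 |
| 2.0 | 0.68 | 0.080 | 81.3% | 84.0% | 0.557 |
| 2.5 | 0.73 | 0.128 | 80.6% | 85.6% | 0.539 |
| 3.0 | 0.76 | 0.170 | 80.6% | 86.9% | 0.523 |

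**Step 3: cross-check by formula.** On the risk-difference scale, power ≈ Φ{0.10 / √[(0.37/300)(1 − R²)] − 1.96}. For R² = 0 this is Φ(2.847 − 1.96) = 81.3%. For R² = 0.080, 0.128 and 0.170 it gives 84.3%, 86.2% and 87.8%, in line with the simulation.

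**Step 4: the same gain in patients.** The evaluable number needed for 80% power is roughly 588·(1 − R²): 571 at an odds ratio per SD of 1.5, 541 at 2.0, 513 at 2.5 and 488 at 3.0.

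**Step 5: the effect measure.** At 30% and 20% the odds ratio without a covariate is (0.20/0.80)/(0.30/0.70) = 0.583. Conditioning on a prognostic score moves it away from 1, to 0.523 at the strong end, although the marginal risks are unchanged. The risk difference stays at 0.10, so the number needed to treat remains 1/0.10 = 10 under the plan's rates.

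**The case against.** The strongest reply is that nothing here is an error. Randomisation is blocked by site, the primary model adjusts for center, and the sample size reproduces. A reader might infer from the missing covariate that the primary test is biased or underpowered. The article does not support that: the center-only test is valid and has about 81% power on the plan's own inputs.

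A reader might also take the loss of power as established, or quote a large figure such as ten points. That needs a correlation of about 0.5 between score and outcome. At a 30% risk, a correlation of 0.48 already corresponds to an odds ratio of 4.0 per SD (AUC 0.80). The article points the other way. Its section on risk factors calls the predictors of PTS poorly understood, names recurrent ipsilateral DVT as the only clearly identified clinical one, and reports no reliable prediction from the site, size or occlusiveness of the initial DVT. Enrollment follows within days of a symptomatic DVT, so the score may largely reflect acute symptoms. It is also not a baseline value of the outcome: PTS is diagnosed by a yes/no symptom definition, and the Villalta scale only grades its severity. All of this stands, and it makes a gain of 0 to 3 points at least as defensible as a larger one.

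Nor is it right that baseline variables reach the secondary models only as differences. Co-morbid conditions that can produce leg complaints, and the initial type of heparin, are named outright. The phrase on differences is condensed, concerns secondary analyses only, and may be spelled out in a fuller analysis plan.

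These points limit the size and certainty of the gain. They do not show a harm from the change. If the score is not prognostic, simulated power is 80.4% against 80.7%, a difference within simulation error.

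**Conclusion.** The point holds as a cheap improvement, not as an error. The article fixes a center-only primary model although a pre-treatment PTS score is collected, and no treatment-effect model names that score. Adjustment would leave power at about 81% if the score is weak, and bring it to about 84% if moderate and 86–87% if strong, with no material loss if it is not prognostic at all.

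The range rests on an assumed odds ratio per SD of 1.0 to 3.0, on 300 evaluable patients per arm, on the plan's event rates, and on simulations without center effects. The documents do not say where in that range the enrollment score lies. The wording on baseline differences is worth replacing at any prognostic strength, because selection by observed imbalance is data-driven and ignores prognostic value.

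**What to change.** Before unblinding:

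- Specify the primary logistic model as treatment, center and the enrollment PTS scale score as a continuous covariate.
- Keep the center-only model as a sensitivity analysis.
- Report a standardised (marginal) risk difference beside the conditional odds ratio, and derive the planned number needed to treat from it.
- Include the same enrollment score in the between-group model for PTS severity.
- Replace the phrase on baseline differences with a list of prespecified baseline covariates. The quality-of-life analysis already does this with age, sex and comorbidity.

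The cost is wording in the analysis plan, with no new patients, visits or data. There are two small downsides. The adjusted odds ratio is conditional and lies slightly further from 1 (0.58 to 0.52 at the strongest effect considered), which is why the standardised risk difference should stand beside it. The few missing enrollment scores need a simple imputation fixed in advance, such as the overall mean.

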### Primary and secondary outcome measures

The primary outcome measure is the incidence of PTS during 2 year follow up. PTS will be diagnosed at the 6 month visit or later if the patient reports pain and swelling of ≥ 1 month's duration that is typical in character (worse at the end of the day or with prolonged sitting or standing, and better after a night's rest and leg elevation), and that is present ≥ 6 months after the acute DVT [52]. Patients diagnosed with PTS will be considered to have reached the study endpoint. Severity of PTS will be graded according to the Villalta scale [53], a clinical post-thrombotic syndrome measure that rates the severity of five patient-rated symptoms and six clinician-rated clinical signs [53]. A Villalta score of 5–9 represents mild post-thrombotic syndrome; 10–14, moderate post-thrombotic syndrome; and > 15 or presence of a venous ulcer, severe post-thrombotic syndrome [53].

Secondary outcomes measures include:

• Reflux: Reflux will be assessed and quantified in a standardized fashion by venous ultrasound [52,56].

• Recurrent VTE: Objective tests and validated algorithms will be used to diagnose recurrent DVT and PE, as described previously [57-59], and all events and deaths will be independently and blindly adjudicated. Death from VTE will be assessed as 'likely' or 'unlikely' after review of the death certificate, patient chart, autopsy report (where available) and by contacting the treating physician.

• Bleeding: Clinically suspected bleeding events will be documented by recording the clinical event and results of any objective diagnostic testing performed. Bleeding will be defined as major if it is clinically overt and associated with a fall in hemoglobin of 20 g/L or a need for transfusion of ≥ 2 units of red blood cells; if it was intracranial or retroperitoneal; or if it warranted the permanent discontinuation of anticoagulation. Less severe clinically overt bleeding which is considered abnormal will be classified as minor.

• Markers of inflammation: C-reactive protein will be assayed using a nephelometric assay. IL-6, IL-8 and MCP-1 will be measured using commercial ELISA kits which include plasma controls (Biosource Europe SA, Nivelles, Belgium). At the time of blood draw for markers of inflammation, data will be recorded on time of day, type and duration of heparin use, concomitant medications and medical conditions.

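### The primary logistic regression ignores follow-up time for a cumulative PTS outcome with 25% projected loss, so the risks, the NNT and possibly the treatment contrast depend on how PTS-free leavers are coded

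*Protocol article*

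**What the plan says.** All references are to the protocol article.

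- **Outcome** (Primary and secondary outcome measures): "The primary outcome measure is the incidence of PTS during 2 year follow up". On timing, "PTS will be diagnosed at the 6 month visit or later if the patient reports pain and swelling". The endpoint is terminal: "Patients diagnosed with PTS will be considered to have reached the study endpoint".
- **Visits** (Table 1): PTS can be recorded at the 6-month, 1-year, 18-month and 2-year visits.
- **Sample size** (Sample size and power calculations): the assumption is that "event rates (i.e. PTS at 2 years) will be 30% in the inactive stocking vs. 20% in the active stocking group"; the number needed "with a two-tailed α of 0.05 and 80% power is 600". Then: "We increased our sample size to 800 to take into account a projected 25% loss-to-follow up by 2 years".
- **Analysis** (Statistical analysis): "An intention-to-treat analytical approach will be used for all outcomes". For PTS, "a logistic regression analysis initially adjusted only for center will be used to compare the incidence rates between the active vs. inactive stockings groups". An NNT is to be calculated. The article names no time-to-event analysis of PTS and does not say how patients lost without PTS enter the model.

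**The concern.** A patient diagnosed at 6 months and lost at 8 months has a known outcome. A patient free of PTS at 6 months and lost at 8 months does not: that patient supplies one negative assessment and nothing more. With 200 of 800 patients projected lost, this is a common situation.

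A yes/no regression cannot use the partial information. Without imputation, once observed events are kept, PTS-free leavers can only be removed from the denominator or counted as negatives. The first pushes risk up and the second pushes it down. The headline risks and the NNT then rest on a coding choice. If one arm loses more patients, the treatment comparison shifts as well, in opposite directions under the two codings.

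**Working it through.** **1. The plan's own figure.** Two-sided α 0.05, power 80%, 30% versus 20%, pooled variance: 294 per arm, 588 in total, within 3% of 600. Power at 300 per arm is 80.9%. Inflation: 600 / 0.75 = 800. The sample size is correct.

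**2. Assumptions not in the article.** Among patients who develop PTS, first diagnosis falls 50/20/15/15% at 6, 12, 18 and 24 months. Loss is spread evenly over 24 months and is unrelated to PTS within arm. There are 400 patients per arm; center adjustment is left out.

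**3. Share of PTS cases diagnosed before loss.** With loss *l* by 24 months, a patient is still present at month *t* with probability 1 − *l*·*t*/24. The share seen is therefore f(*l*) = 1 − k·*l*, where

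k = 0.50×0.25 + 0.20×0.50 + 0.15×0.75 + 0.15×1 = 0.4875.

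For true risk *p*:
- leavers coded as no PTS: *p*·f
- PTS-free leavers dropped: *p*·f / [*p*·f + (1 − *p*)(1 − *l*)]

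**4. Equal 25% loss, true 30% versus 20%.** f = 1 − 0.4875×0.25 = 0.878.

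| Coding | Inactive | Active | Difference | OR | NNT |
|---|---|---|---|---|---|
| Truth | 30.0% | 20.0% | 10.0 points | 0.583 | 10.0 |
| Drop | 0.2634/(0.2634+0.525) = 33.4% | 0.1756/(0.1756+0.600) = 22.6% | 10.8 | 0.583 | 9.3 |
| Code as no PTS | 26.3% | 17.6% | 8.8 | 0.596 | 11.4 |

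Simulation (4,000 trials) agrees within about 0.1 point: 33.5% versus 22.6% and 26.4% versus 17.5%; the life-table estimate gave 30.0% versus 19.9%.

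**5. No true effect (30% in both arms), unequal loss.** Loss 20% inactive, 30% active: f = 0.9025 and 0.85375.
- Code as no PTS: 27.1% inactive versus 25.6% active, 1.46 points in favour of active. SE = √(0.2634×0.7366×2/400) = 0.0311, shift 0.47 SE, type I error = 1 − Φ(1.49) + Φ(−2.43) ≈ 7.6%.
- Drop: 32.6% versus 34.3%, 1.74 points against active, shift 0.46 SE, type I error about 7.5%.

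Simulated: 7.8% (drop) and 7.7% (code as no), against 4.5% for the life-table/log-rank test. At 15% versus 35% the same formulas give 15.3% and 15.5%; simulated 15.4% and 14.8%, against 4.5%.

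**6. True effect, loss 20% inactive and 30% active.** Drop: 23.4% / 32.6%, RR 0.72. Code as no PTS: 17.1% / 27.1%, RR 0.63. Truth: 0.67. Simulated rejection rates: 72%, 93%, and 86% for the life-table/log-rank test.

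**7. Sensitivity to onset timing.** With onset 25/25/25/25%, k = 0.625. Type I error is then 6.4% (drop) and 9.4% (code as no) at 20% versus 30%, and 10.8% and 23.0% at 15% versus 35%.

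**8. Why the life table recovers the truth here.** Interval hazards use only patients still followed, so loss unrelated to PTS cancels. For the inactive arm, survival is 0.85 × (0.79/0.85) × (0.745/0.79) × (0.70/0.745) = 0.70, whatever *l* is.

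**9. Enough patients for the alternative.** HR = ln 0.8 / ln 0.7 = 0.626. Events needed: 4(1.96 + 0.84)² / (ln 0.626)² ≈ 143 (Schoenfeld), or 148 (Freedman). With exponential 25% loss and a constant PTS hazard from 6 to 24 months, 800 patients yield about 67 + 101 = 168 events and about 86% power.

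**The case against.** **The rule for leavers may sit in the analysis plan.** An article may leave missing-outcome handling to a fuller document, and multiple imputation within logistic regression is a third route. This stands, so the missing rule is not itself the fault. What remains is that the article has already named a primary model without follow-up time for a staged cumulative outcome with heavy projected loss.

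**At equal loss the contrast hardly moves.** Correct: the OR is 0.583 or 0.596 against 0.583. The damage there is to the absolute risks and the NNT. Type I inflation needs unequal loss, and the article gives no loss by arm. The difference in ankle pressure does not establish it either: stopping the stockings is not the same as leaving follow-up, and the stockings look identical.

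**Stronger readings that a reader might infer.**
- *The analysis is not intention-to-treat.* Not established. The article declares the principle, a logistic model does not decide who enters it, and inflating 600 to 800 does not define an analysis set.
- *The result is biased whenever loss differs by arm.* Too strong. With 2-year completers only and loss unrelated to PTS within arm, the OR stays 0.583 even at 35% versus 15% loss (though this discards PTS already diagnosed in later leavers). Conversely, equal but informative loss can bias it: with 25% lost in each arm and 30% risk in all leavers, active completers have (0.20 − 0.25×0.30)/0.75 = 16.7% against 30%, OR 0.467.
- *The sample-size and outcome sections describe different quantities.* They do not conflict. PTS at 2 years, with diagnosis as a terminal endpoint, reads naturally as cumulative incidence by 2 years.

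**The remedy wins on its own assumption.** The calculations generate non-informative loss, which is what the time-to-event model requires. This stands as a limit on the remedy.

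**Conclusion.** The concern holds in conditional form. The named primary model cannot use partial follow-up, and without imputation the two codings that keep observed PTS events err in opposite directions. At the protocol's own 25% loss, taken as equal in both arms, the NNT is about 9 or 11 instead of 10, with little effect on the OR. If loss differs by arm, type I error is about 8% at 20% versus 30% and about 15% at 15% versus 35%; under even onset the ranges are about 6–9% and 11–23%. Loss by arm, loss timing and onset timing are all assumptions. The sample size is not at fault. This is a worthwhile improvement to the primary analysis, not a defect that invalidates the trial.

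**What to change.** - **Primary analysis:** a discrete-time model (complementary log-log link, visit-specific baseline) or an interval-censored proportional hazards model, adjusted for center, with PTS-free patients censored at their last PTS assessment.
- **Absolute measures:** take the 2-year risks, their difference and the NNT from life-table estimates, with death treated as a competing event.
- **Sensitivity analysis:** keep the center-adjusted logistic regression, with multiple imputation of missing PTS status.

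**Cost:** a change of analysis wording. PTS status by visit is already collected, and 800 patients suffice.

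**Downside:** the model assumes non-informative censoring within arm. Patients lost before the 6-month visit still contribute no PTS information, because PTS cannot be diagnosed before then.

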### Risk factors for the development of PTS

While hereditary and acquired risk factors that predispose to the development of VTE are widely known [6], factors that influence the development of PTS after DVT have not been well elucidated. The only clearly identified clinical risk factor for PTS is recurrent, ipsilateral DVT [7,8]. The site (proximal vs. distal), size and occlusiveness of the initial DVT and the intensity (i.e. target INR) of long term anticoagulation for DVT do not appear to reliably predict PTS [1,7-10]. It is not clear why some patients develop PTS while others recover from their DVT. As a result, physicians are unable to provide their DVT patients with reliable, individualized prognostic information.

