Study patients are followed for 2 years after enrollment. The procedures at each visit are shown in Table 1. At any time during the study, if a patient has symptoms or signs suggestive of recurrent VTE, he contacts the study team for medical assessment, at which time recurrent VTE will be ruled in or ruled out. Similarly, if an adverse event occurs, the patient contacts the study team for evaluation. If a patient withdraws from the study, a Study Termination form is completed to account for withdrawal, which will document the reason(s) for withdrawal. If a patient dies, a Death Form is completed which documents the cause(s) of death, further classified as VTE likely or unlikely. Throughout study follow-up, co-interventions are recorded (e.g. diuretics, analgesics, exercise). While not encouraged, any temporary use of elastic bandages/wraps or active stockings during the acute phase of DVT is systematically tracked.

**Table 1 T1:** Details of study visits and telephone calls

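### Secondary adjusted models and three subgroup analyses of the stocking comparison condition on post-randomisation variables, which can bias those estimates; the primary analysis is unaffected

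*Protocol article*

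**What the plan says.** The primary analysis, in the Statistical analysis section of the protocol article, is "a logistic regression analysis initially adjusted only for center will be used to compare the incidence rates between the active vs. inactive stockings groups", under intention to treat.

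For secondary analyses of the same comparison the section states: "other covariates that will be adjusted for are duration of anticoagulation with warfarin, recurrent ipsilateral DVT during follow-up, temporary use of active stockings". The list continues with "initial type and duration of heparin anticoagulation, co-morbid conditions that could lead to leg symptoms/signs and differences in pertinent baseline variables".

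On subgroups it states: "Subgroup analyses by age, sex, level of compliance, duration of warfarin anticoagulation and recurrent VTE during study follow-up are also planned".

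Three other places bear on these choices:

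- **Recurrence as an outcome.** The Statistical analysis section compares recurrence between arms: "For the secondary outcomes valvular reflux, recurrent VTE, death from VTE, venous ulcer, major bleeding, and severity of PTS, rates in the two intervention groups" are to be described and then explored by regression. Aims of the study also lists recurrent DVT by arm among the secondary aims.
- **Recurrence as a cause of PTS.** Risk factors for the development of PTS states: "The only clearly identified clinical risk factor for PTS is recurrent, ipsilateral DVT".
- **Timing.** Table 1 first records stocking compliance on the follow-up form at the 1-month visit. Study procedures says that "any temporary use of elastic bandages/wraps or active stockings during the acute phase of DVT is systematically tracked".

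**The concern.** Randomisation makes the arms comparable at baseline. A model or subgroup keeps that comparability if it conditions on baseline variables. It can lose it if it conditions on something that the assigned stocking may have changed.

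The plan treats recurrence both as something stockings may influence (an outcome by arm) and as something to hold constant (a covariate and a subgroup factor). If stockings prevent some PTS by preventing recurrence, adjustment takes that part of the benefit out of the estimate. If an unmeasured factor drives both recurrence and PTS, adjustment also links that factor to treatment arm, and this can produce an apparent effect where none exists.

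Compliance raises the second problem. Active stockings exert 30–40 mm Hg and inactive ones 5 mm Hg (Current trial design), and PTS is diagnosed from reported pain and swelling (Primary and secondary outcome measures). Who keeps wearing the stocking may therefore depend on both the arm and the state of the leg. Compliers on active stockings and compliers on inactive stockings would then be differently selected patients.

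What is at stake is how the secondary results are read. After a null primary result, an apparent benefit in compliers could be taken as evidence for stockings without any treatment effect behind it. After a positive result, adjustment for recurrence could understate the benefit.

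**Working it through.** **1. The plan's own figures.** No figure is disputed; this confirms the frame. With 30% vs 20%, two-sided α 0.05 and 80% power (Sample size and power calculations), pooled variance:

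n per arm = [1.96·√(2·0.25·0.75) + 0.8416·√(0.30·0.70 + 0.20·0.80)]² / 0.10² ≈ 293.2, so 294 per arm and 588 in total, within 3% of the stated 600. Then 600 / 0.75 = 800, as stated. Nothing below changes these numbers.

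**2. When each variable is fixed.**

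| Variable | Use in the plan | Timing |
|---|---|---|
| Recurrent ipsilateral DVT in follow-up | covariate | after randomisation, by its definition |
| Recurrent VTE in follow-up | subgroup | after randomisation, by its definition |
| Compliance level | subgroup | after randomisation (first recorded at 1 month) |
| Warfarin duration | covariate, subgroup | completed after randomisation |
| Temporary active-stocking use | covariate only | acute phase; may fall before or after randomisation |
| Heparin duration | covariate | may run past randomisation |
| Age, sex | subgroup | baseline |

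**3. Whether conditioning can distort the estimate.** The documents give no recurrence or compliance rates, so every input here is an assumption. Large-sample simulation, 2,000,000 subjects per scenario, with arm A, standard normal unmeasured cause U, post-randomisation variable R and outcome PTS:

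- logit P(R) = logit(0.12) + b1·A + b2·U
- logit P(PTS) = logit(0.25) + b3·A + b4·R + b5·U

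Each row gives exp(b) for the assumed links, then the odds ratio (OR) for arm without and with R in the model.

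| Scenario | A→R | U→R | A→PTS | R→PTS | U→PTS | OR without R | OR with R |
|---|---|---|---|---|---|---|---|
| (a) Arm does not affect R | 1 | 1 | 0.583 | 3 | 1 | 0.591 | 0.580 |
| (b) Whole effect runs through R | 0.5 | 1 | 1 | 6 | 1 | 0.895 | 1.004 |
| (c) Direct effect, R and shared cause | 0.5 | 2 | 0.55 | 3 | 2 | 0.546 | 0.591 |
| (d) No effect on PTS, shared cause | 0.5 | 2 | 1 | 1 | 2 | 1.002 | 1.030 |
| (e) As (d), stronger links | 0.3 | 2.5 | 1 | 1 | 2.5 | 1.000 | 1.073 |

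Within subgroups defined by R (present, absent) the arm ORs were 0.599 and 0.590 in (c), 1.048 and 1.028 in (d), and 1.093 and 1.070 in (e). In (a) the small shift is non-collapsibility of the odds ratio, not bias.

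**4. Compliance under no treatment effect.** Assume 77% comply on placebo and 59% on active, and active wearers with worse legs stop more often. Simulation (400,000 subjects) gave an OR of 0.85 among compliers (0.78 to 0.92 over the range tried) and 1.24 among non-compliers (1.14 to 1.36). As a check by numerical integration, OR = odds{E[C₁Y]/E[C₁]} / odds{E[C₀Y]/E[C₀]}, where Y is PTS risk and C₁, C₀ the probability of complying on active and placebo. With PTS 30% in both arms, U doubling the odds of PTS per SD, and U halving the odds of complying on active only, this gives 0.84 and 1.26. If U also lowers compliance on placebo (OR 0.67 per SD), it gives 0.89 and 1.04. The sign among compliers here is opposite to (e), because the assumed direction of selection differs.

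**5. Scale against sampling error.** At 30% vs 20% with 300 per arm, SE(log OR) = √(1/90 + 1/210 + 1/60 + 1/240) = 0.19. The shift in (b) is ln(1.004/0.895) = 0.115; in (c) it is ln(0.591/0.546) = 0.079. In these recurrence scenarios the distortion is well below one standard error.

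**The case against.** The strongest reply is that none of this reaches the trial's main conclusion. The primary model adjusts for centre only, the disputed models are expressly secondary, and the per-protocol analysis is described as explanatory and as an adjunct. No sample size or interim boundary depends on them. This stands, and it sets the severity.

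Second, bias requires allocation to affect the variable. Scenario (a) shows none otherwise. For warfarin duration the documents name no path from stocking to treatment length, and study personnel are blinded. This stands: the case there is less certain.

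Third, the article's account of how stockings work is calf-pump assistance with less venous hypertension and reflux, not prevention of recurrence. A wholly mediated effect as in (b) is therefore an extreme case, and (c) shows attenuation rather than reversal. This also stands.

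Fourth, temporary stocking use belongs to the acute phase. Patients may enter up to 10 days after diagnosis, and study stockings arrive a few days after enrolment, so some use may precede randomisation. It is also not a subgroup factor. Only use after randomisation is open to the objection.

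Fifth, a reader might add the adjustment for "differences in pertinent baseline variables" to the charge. That is not conditioning on a post-randomisation variable. How such covariates are chosen is a separate, lesser question, and the rule may lie in an analysis plan that is not shown.

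The reply does not remove the core. The text commits to adjusting for follow-up recurrence and to subgroups by compliance and recurrence, and it does not mark these as mediation or adherence analyses.

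**Conclusion.** The point holds at moderate severity, for secondary analyses only. As written, the secondary adjusted models and the compliance, warfarin-duration and recurrent-VTE subgroups can give estimates that should not be read as effects of the randomised stocking. The case is clearest for recurrence and compliance, weaker for warfarin duration, and partial for temporary stocking use.

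It rests on two assumptions: that allocation may influence the variable, and, for the bias through shared causes, that an unmeasured factor affects both that variable and PTS. The article supports the first for recurrence by making it an outcome by arm. For compliance both are plausible, given the pressure difference and the symptom-based diagnosis.

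Neither size nor direction can be derived from the documents; the figures above only demonstrate the mechanism. A reader might infer that the trial's treatment effect is biased, or that these analyses will reverse it. The documents support neither: the primary analysis is untouched, and reversal needs extreme or specially chosen inputs. The age and sex subgroups are sound. The biomarker models that include recurrent DVT address prognosis and are outside this point.

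**What to change.** For every analysis presented as a treatment comparison, restrict covariates and subgroup factors to variables fixed at or before randomisation. Table 1 shows that the enrolment visit already collects demographic and clinical variables, DVT test results, the PTS scale and the pain scale; which of these to use is for the investigators to settle in advance.

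Report recurrence as an outcome by arm. Report warfarin duration, temporary stocking use and compliance by arm, descriptively.

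If a mediation or adherence effect is wanted, present it as a separately labelled analysis with its assumptions stated. One example is a complier-average causal effect with randomisation as instrument, stating the exclusion restriction and the cut-off that turns level of compliance into complier status.

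The cost is wording: no new data, no change to the 600 or 800, and no change to the primary model. The downside is that the listed adjusted and subgroup results based on post-randomisation variables would no longer be presented as treatment effects.
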